**C. PRELIMINARY STUDIES**

This is a feasibility trial based on conversations with colleagues in the field of exercise oncology. There is a major gap in the literature of well-designed RCT’s combining resistance exercise and nutrition as an intervention for sarcopenic individuals after treatment for colorectal cancer. Importantly, one of the biggest gaps in the field of exercise oncology is the lack of interventions targeting treatment-related impairments, that specifically enroll individuals with an impairment.^25,76,77^ Our trial will be one of the first to address this gap by objectively characterizing individuals as sarcopenic, prior to enrollment. This will advance the field by furthering our understanding of the feasibility and challenges of implementing lifestyle interventions to individuals with sarcopenia after colorectal cancer treatment.

Despite strong evidence from other populations supporting the potential of combining resistance exercise and creatine supplementation to improve physiologic and QOL outcomes that cancer treatments adversely affect, evidence specific to cancer remains scarce. ^44,55,78-81^ Critical first questions in this line of inquiry are: 1) if individuals who are sarcopenic after treatment for colon cancer can be recruited to lifestyle interventions; and 2) is our proposed intervention combining resistance exercise and creatine supplementation feasible for this population. We contend the proposed study is innovative in that it would be the first to implement and test this evidence-informed intervention in individuals who are sarcopenic after colon cancer. The proposed RCT builds on several aspects of our team’s prior research investigating the effectiveness of resistance exercise, diet and creatine supplementation in older adults and individuals with cancer.^29,82-84^ Additionally, we have an ongoing RCT with creatine supplementation in prostate cancer that has been delayed due to COVID-19.^82^ However, we have recruited 30 individuals so far, with no adverse events, and we have demonstrated the safety, feasibility and tolerability of supplementation in other cancer populations. Members of our team have investigated the molecular regulators of skeletal muscle mass and how they impact the response to exercise and nutrition interventions.^85-87^ Moreover, we have adhered to NIH guidelines on pilot studies and framework for clinical research, with a focus on obtaining data to optimize the intervention procedures and inform the design of a future randomized controlled trial.^88,89^

**D. RESEARCH DESIGN AND METHODS AND DATA ANALYSIS**

**Location:** Pre- and post-intervention data collection and exercise sessions take place at the University’s Department of Exercise Science.

**Intervention: *Resistance Exercise Training****.* Participants assigned to each arm will attend a total of 30 supervised exercise sessions for 10 weeks (thrice weekly, with a minimum 48 hours rest between sessions). This intervention is commonly employed in exercise oncology and has yielded high rates (~80%) of attendance and has not resulted in any adverse events.^18,24,27,28,90-94^ All exercise sessions will occur in the Sports Science Lab at the University of South Carolina, supervised by members of the research team specifically trained in exercise oncology. For the intervention, participants will be asked to perform 8 total movements targeting total body musculature. The exercise selected to target each of these movements will be multi-joint, compound movements, tailored to each participant in accordance with the clinical judgement of trained study staff in the trial. Sessions will be progressed by adding sets to the exercises and increasing load as appropriate and tolerated (i.e. in exercises where no load can be added, a focus will be on adding sets). Specifically, trained exercise physiologists in the trial will select the appropriate exercises, providing coaching cues for safe movement and tailored exercise sessions. **Intervention Fidelity:** Exercise intervention fidelity will be reported using metrics previously outlined by [name] et al (2019).^24^ Specifically, volume load will be calculated as a function of sets x reps x weight for each exercise and summed to give total volume for each session. We will report the proportion of volume achieved relevant to what was prescribed to give a “relative-dose intensity” (RDI) for each person. RDI will then be averaged and used to determine fidelity to the RT intervention.

**Supplementation.** Participants in the creatine group will receive creatine monohydrate supplementation (Optimum Nutrition, USA) at a dose of 0.10g/kg/day. This dose has been used in RCT’s involving older adults and individuals with cancer.^82,83^ Participants in the placebo group will receive a creatine placebo supplement (corn-starch maltodextrin; *Bulk Supplements, Nevada, USA*) in the same dose and schedule as EXSUPP. Participants will be instructed to consume 0.05g/kg/day of their supplement with food in the morning and 0.05g/kg/day with food in the afternoon or evening. Both groups will have similar flavor supplements to mask taste and solubility. **Supplement Adherence:** Supplements will be provided using smart-pill bottles (Pillsy, Inc; Seattle, WA), that will be used to automatically track number of times bottles are opened and return estimates of compliance to supplementation. The smart-pill bottles are accompanied by an app, which tracks when the bottle is opened, tracks remaining doses and has reminders/alarms for missed doses. For adherence, it is assumed that opening the bottle cap signifies consumption of a daily dose. As such, adherence to supplementation will be quantified as number of daily doses consumed across the intervention, relative to what could have been consumed. The reliability of smart pill bottles to track medication adherence has been published recently and has been demonstrated to improve adherence in cancer.^95-97^

**Study Outcomes:** Study outcomes will be assessed within 1 week of initiation and completion of the intervention.

**Primary Outcome:** The primary outcome of feasibility will be evaluated by **Response rates** (cases responding/cases ascertained (minus letters returned/not delivered & disconnected phone lines), and **reasons for ineligibility/disinterest** **and proportional accrual** (cases enrolled/cases ascertained) will all be tracked to inform feasibility of the trial. **Retention** will be calculated as the proportion of individuals who return for follow-up testing. **Adherence** will be calculated as proportion of total exercise achieved (outlined in “Intervention Fidelity”), and proportion of daily supplementation taken. **Adverse events** will be recorded, including a description of the event, its relation to the intervention, level of seriousness and intensity. To better understand program feasibility and acceptability, individuals will be asked to participate in qualitative in-depth exit interviews at the end of the study. A semi-structured interview guide will include questions that prompt participants to elaborate on their experiences and perceptions of the program and suggestions for how the program can be improved. Interviews will be audio-recorded, transcribed verbatim, and coded using inductive thematic analysis with Nvivo software(QSR International, Burlington, MA; USA).

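### Supplement adherence counts a bottle opening as a full daily dose although the day's supplement is taken in two halves, so read literally the measure is overstated by up to two-fold

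*Protocol*

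**What the plan says.** Protocol section D, under Supplementation, gives creatine "at a dose of 0.10g/kg/day" and tells participants to "consume 0.05g/kg/day of their supplement with food in the morning and 0.05g/kg/day with food in the afternoon or evening". Placebo is given "in the same dose and schedule as EXSUPP", so both arms have two intakes a day.

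Under Supplement Adherence, smart bottles "automatically track number of times bottles are opened and return estimates of compliance to supplementation". The scoring rule follows: "it is assumed that opening the bottle cap signifies consumption of a daily dose". Adherence is "quantified as number of daily doses consumed across the intervention, relative to what could have been consumed".

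Under Primary Outcome, the paragraph that begins "The primary outcome of feasibility will be evaluated by" includes the "proportion of daily supplementation taken". Section A (Specific Aims) sets at least 75% adherence to creatine or placebo as one of the feasibility targets and makes trial success depend on meeting the feasibility outcomes.

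The protocol does not say that an opening stands for a half-dose, that two openings are expected each day, or how a second opening on the same day is treated.

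**The concern.** The schedule and the scoring rule use different units. A participant who follows the instructions has two intakes a day, each of half the daily amount. The rule credits an opening with the whole daily amount and sets the total against daily doses. Someone who takes only the morning half every day would be scored as fully adherent.

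What is at stake is an absolute threshold. Supplement adherence is one of the measures that decide whether the pilot is called feasible, and the pilot is meant to inform the design of a larger trial. An inflated figure could let the 75% target be met when the amount actually taken is well below 75% of that assigned.

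**Working it through.** The protocol gives no worked adherence figure, so there is none to reproduce. The check applies the stated rule to the stated schedule.

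**Inputs**
- Duration: 10 weeks (section D, Intervention). Assuming supplementation on every day, 10 x 7 = 70 days.
- Intakes per day: 2 (section D, Supplementation), so 2 x 70 = 140 scheduled half-doses.
- Target: at least 75% (section A).

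**Definitions**
- Share of assigned amount taken = half-doses taken / 140, with one half-dose per opening.
- Reading (a), day-level: a day with at least one opening counts as one daily dose; score = such days / 70.
- Reading (b), every opening: each opening counts as one daily dose, with no cap; score = openings / 70.

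**Openings needed to reach the target**
- 0.75 x 70 = 52.5, so 53 openings on 53 different days are enough under either reading.
- Score: 53/70 = 75.7%. Share taken: 53/140 = 37.9%.
- Counted in half-doses, the target needs 0.75 x 140 = 105.

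**Intake patterns**

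Where both probabilities lie strictly between 0 and 1, the two intakes are assumed independent, and the score under (a) is 1 - (1 - p_morning)(1 - p_evening). The share taken is (p_morning + p_evening)/2, and the score under (b) is p_morning + p_evening.

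| p_morning, p_evening | Share taken | Score (a) | Ratio (a) | Score (b) | Ratio (b) |
|---|---|---|---|---|---|
| 1, 1 | 100% | 100% | 1.0 | 200% | 2.0 |
| 0.75, 0.75 | 75% | 93.8% | 1.25 | 150% | 2.0 |
| 0.9, 0.5 | 70% | 95% | 1.36 | 140% | 2.0 |
| 0.5, 0.5 | 50% | 75% | 1.5 | 100% | 2.0 |
| 1, 0 | 50% | 100% | 2.0 | 100% | 2.0 |
| 0.75, 0 | 37.5% | 75% | 2.0 | 75% | 2.0 |

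Under (a) the ratio depends on behaviour and lies between 1 and 2. Under (b) it is always 2, because the numerator counts half-doses as whole ones. For example, two openings on 38 days give 76/70 = 109% scored against 76/140 = 54% taken.

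Capping the count at one per day, which turns (b) into (a), therefore does not cure the problem. It removes scores above 100% but leaves the two-fold overstatement for anyone who takes one half-dose a day.

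**The case against.** The strongest reply is that a daily dose may have been meant as either of the two doses scheduled for the day. The protocol uses per-day wording loosely, since it labels each half-intake per day as well, and its denominator is whatever could have been consumed, not 70. If doses mean scheduled intakes, numerator and denominator are both on a basis of 140 and the split inflates nothing. The app, which logs opening times and alerts the participant to missed doses, would fit such scoring. This reading is possible, but it is stated nowhere, and the Primary Outcome paragraph again speaks of daily supplementation. A measure that can be divided by 70 or by 140 still needs correcting.

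It can also be said that counting details belong in a statistical analysis plan, which may exist. But the protocol does not leave the rule open. It fixes one, and that rule conflicts with its own schedule.

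Several limits do stand:
- Two-fold is the worst case under the day-level reading, and nothing in the protocol suggests that taking one half a day will be common.
- Scores above 100% need uncapped counting and would be noticed at once.
- A participant who takes both portions out at one opening is scored correctly by the day-level rule.
- Dose schedule and counting are identical in the two arms.

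A reader might infer that individual participants will be passed at 38% intake, or that the pilot will be declared feasible in error. The protocol does not support that. It states no pass rule for individuals, and exercise fidelity is averaged across participants. If supplement adherence is averaged too, a sample figure of 75% would conceal 38% intake only if participants in general took one half-dose on each counted day. Nor does the point show bias in the strength comparison.

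**Conclusion.** The point holds as a conflict between the scoring rule and the dosing schedule. Taken literally, the supplement-adherence component is overstated: by a factor between 1 and 2 if days with any opening are counted, and by exactly 2, with scores up to 200%, if every opening is counted. The lowest intake that can meet the 75% target is 53/140 = 37.9% of the assigned amount.

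These figures assume 70 days of daily supplementation and one half-dose per opening. They cover only the effect of the split; openings without intake would be a separate source of error. The consequence is confined mainly to the absolute 75% criterion and to the adherence figure passed on to the larger trial. If the investigators in fact meant one opening per scheduled half-dose with 140 expected, there is no inflation from the split, and the remedy is to say so.

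**What to change.** Rewrite the Supplement Adherence definition in half-doses. Credit at most one opening in each of two daily windows (morning; afternoon or evening), using the opening times that the app already records. Divide by the scheduled half-doses, 2 x 70 = 140. State the clock time that separates the windows. Use the same definition under Primary Outcome and apply the 75% target in section A to it, so that the target corresponds to 105 of 140 half-doses.

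The cost is some rewording and a different summary of data already collected; dose, schedule and trial conduct are untouched. There are two drawbacks. Reported adherence may be less favourable. A participant who takes both portions out at one opening will be credited with only one of them, which should be acknowledged when the result is reported. The change is best made before any adherence data are summarised.

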**Principal Investigator Name: [name]**

**A. SPECIFIC AIMS**

We seek to conduct a pilot RCT, examining the effects of a 10-week multimodal resistance exercise and creatine intervention (EXSUPP) (n=20) relative to resistance exercise and creatine placebo (EXPLA) (n=20) in sarcopenic individuals who have previously been treated for colorectal cancer. **Our overarching objectives are** to **1)** determine the feasibility and acceptability of the EXSUPP intervention with **creatine monohydrate supplementation** (0.10 g/kg/day) and **2)** understand the intervention characteristics that can be used to inform the design of a future large RCT. **Our RCT is *significant* because** it will establish the feasibility and acceptability of combining creatine monohydrate with resistance exercise training in the management of sarcopenia in individuals with colorectal cancer, providing preliminary support for the integration of effective lifestyle interventions in the management of colorectal cancer care. This pilot RCT will provide important information for the design of a future large-scale RCT R01 submission. To test our hypothesis and achieve the application objectives, we propose the following ***Specific Aims*:**

**Primary Aims: 1(a) To explore the feasibility and acceptability of a 10-week RCT comparing EXSUPP to EXPLA in individuals who are sarcopenic after colorectal cancer treatment.** This aim will be accomplished by assessing accrual, retention, adherence, and adverse events, **and 1(b) to quantify (mean change scores and precision estimates) and compare between-arm differences in muscular strength,** the primary variable used to diagnose sarcopenia.^2^ We hypothesize that we will be able to recruit (within a 12-month window) 40 colorectal cancer survivors, retain ≥75% of the sample, and achieve ≥75% adherence to the resistance exercise intervention and ≥75% adherence to creatine/creatine placebo supplementation, with no adverse events experienced throughout the intervention. For aim 1(b), we hypothesize that the EXSUPP arm will experience a more favorable muscle strength response than the EXPLA arm following the intervention. The trial will be considered a success if feasibility outcomes are achieved, and the hypothesized directionality of the EXSUPP intervention effects on muscular strength is observed.

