A convenience sample (n=40) will be recruited to determine the feasibility of the intervention. The rationale for this is in line with recommendations from Julious et al (2005) that justify an n=12 as a minimum based on feasibility, gains in precision surrounding the mean and variance, and ability to estimate parameters for future studies.^103^ Consequently, given that our study has two arms, and in line with other exercise oncology trials in anticipation of an ~75% retention rate, we aim to recruit 20 individuals per arm to participate in full study activities.

2. RECRUITMENT PLANS:

Recruitment will occur in collaboration with two healthcare partners (PRISMA Health and South Carolina Oncology Associates, [SCOA]). SCOA is a medical and radiation oncology practice affiliated with an ACOS-approved Integrated Network Cancer Program in central South Carolina. PRISMA Health-Midlands provides multidisciplinary cancer care in Columbia that is a part of the larger PRISMA Health system. Participants will be recruited by 1) use of cancer registry data bases at local health care system’s cancer programs to prepare personalized invitations, and 2) outreach with various cancer support groups and organizations. We will also request a partial HIPAA waiver from the cancer clinics to recruit from patient lists of contact information. Specifically, the covered entity (Prisma), will provide us with a secure list of individuals previously treated for colorectal cancer, and their PHI. This is one of our strongest methods of recruitment and are currently using it in several ongoing studies. From these lists, we will send an initial introductory letter to eligible patients from their oncology provider with information about the study. There will be a number to call if they do not wish to be contacted by study personnel. After a wait time ~ 2 weeks, study staff will begin contacting the list of potential participants. At initial contact, study recruiters will provide a detailed account of the study and its procedures, answer any questions, ascertain interest, and, if interested, schedule the baseline visit.

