Participants will also be offered a $50 incentive to receive an optional muscle biopsy at each assessment timepoint. Therefore, the total rumination for participants who complete both timepoints and receive a muscle biopsy at each timepoint is $200.

9. WITHDRAWAL:

Participants will be informed that their participation in this research is completely voluntary and made to understand that they are allowed to withdraw from the study from any time, without justification. All participants will be asked to inform a member of the study team of their decision and reason to withdrawal but will be informed that their withdrawal will not affect their relationship or any future opportunities to participate in research with the university. No additional information will be collected after an individual withdraws, through data collected up until the point of withdrawal will be used in analyses and interpretation of results.

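### The exit interviews, the only source of participants' views on the programme, cannot reach those who withdraw

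*Protocol*

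**What the plan says.** Protocol section A (Specific Aims) words primary aim 1(a) as "To explore the feasibility and acceptability of a 10-week RCT comparing EXSUPP to EXPLA", and continues: "This aim will be accomplished by assessing accrual, retention, adherence, and adverse events". The interviews are not named there.

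Protocol section D (Primary Outcome) defines those feasibility measures and then adds, for a fuller understanding of both feasibility and acceptability: "individuals will be asked to participate in qualitative in-depth exit interviews at the end of the study". The interview guide is to draw out participants' experience of the programme and their ideas for improving it. The recordings are transcribed and coded by inductive thematic analysis.

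Protocol section E, item 9 (Withdrawal) states three things that matter here:
- "No additional information will be collected after an individual withdraws"
- "All participants will be asked to inform a member of the study team of their decision and reason to withdrawal"
- "data collected up until the point of withdrawal will be used in analyses and interpretation of results"

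The same item lets participants leave without giving a justification.

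Protocol section E, item 1 (Target Population) sets 20 per arm, 40 in all, "in anticipation of an ~75% retention rate". Section A counts retention of 75% or more as meeting the target.

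**The concern.** Retention, adherence and adverse events record what participants did and what happened to them. They do not record what participants thought of the training or the supplement. In this plan only the interview does that.

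The interview is timed at the end of the study, and the withdrawal rule closes data collection when someone leaves. The group most likely to have found something unacceptable is therefore the group that is not interviewed. The trial can meet its retention target with a quarter of the sample in that position.

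What is at stake is mainly the second overarching objective in section A: learning which features of the intervention should shape the larger trial. Advice on what to change would come mostly from people for whom the programme worked well enough to stay. Later analysis cannot repair this, because an interview that was not held cannot be recovered.

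**Working it through.** **Inputs (all from the Protocol)**
- Planned enrolment: 20 per arm, 40 in total (section E, item 1).
- Anticipated retention: about 75% (section E, item 1). Retention target: at least 75% (section A).
- Interview timing: end of the study (section D, Primary Outcome).
- After withdrawal: nothing further collected. At withdrawal: a reason is requested. Before withdrawal: data kept and used (section E, item 9).

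**The plan's own figure.** The sample size is described as a convenience sample, with 12 as a cited minimum, which I read as per arm. With 20 per arm and 75% retention, 20 × 0.75 = 15 per arm remain, which is at least 12. Inflating 12 for 25% loss would give 12 / 0.75 = 16, so 20 is above that figure and is not presented as a calculated result. This point disputes none of these numbers.

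**How many cannot be interviewed.** Assume that every loss is a withdrawal. Then the number not reached = 40 × (1 − retention).

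| Retention | Can be interviewed | Not reached |
|---|---|---|
| 75% | 40 × 0.75 = 30 | 40 × 0.25 = 10 |
| 80% | 40 × 0.80 = 32 | 40 × 0.20 = 8 |
| 90% | 40 × 0.90 = 36 | 40 × 0.10 = 4 |

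For a given retention these are upper limits on the number shut out by the withdrawal rule. Someone who misses follow-up testing without withdrawing is not barred from the interview by item 9.

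**What each source captures for a participant who withdraws**

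| Source | Captured? |
|---|---|
| Accrual | Yes |
| Retention | Yes, counted as not retained if they do not return for testing |
| Adherence and adverse events | Yes, up to withdrawal |
| Reason for leaving | Requested, but not obligatory |
| In-depth interview | No |

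Only the last row is empty, and that row is the one source of participants' views on the programme.

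**The case against.** The strongest reply is that aim 1(a) does not rest on the interviews. Section A says the aim is met through accrual, retention, adherence and adverse events, and all four include people who leave. The interviews are an addition meant to deepen understanding. The success rule in section A uses the feasibility outcomes and the direction of the strength effect, with no interview criterion. This stands. A reader might infer that acceptability is judged by completers alone, and the documents do not support that. Withdrawers lower retention, their earlier data are used, and they are asked why they left.

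A second reply concerns size. A reader might want to express the problem as an acceptability rate biased upward by so many percentage points. The plan produces no such rate: the analysis is thematic and no acceptability threshold is set. This also stands. The effect is on whose views are heard, and only the number of people not interviewed can be calculated.

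A third reply concerns stopping the intervention. A reader might infer that the withdrawal rule treats stopping the exercise or supplement as leaving the study, so that such participants are lost to the strength comparison in aim 1(b). Item 9 does not say this; it concerns leaving the research. Section E, item 5 (Potential Risks) foresees supplementation being stopped or exercise being modified without calling either a withdrawal. The protocol does not spell the distinction out, but a loss to aim 1(b) cannot be read from that silence.

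Finally, the end of the study could be read as each participant's own end, and stopping collection respects the decision to leave. Even on that reading, item 9 permits nothing after withdrawal and no interview is scheduled before it takes effect. A requested reason, which may be withheld, is much thinner than a semi-structured interview. An interview held only with the participant's agreement does not override the decision to leave.

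**Conclusion.** The point holds in a limited form. The exit interviews are the only source of participants' views on the programme and the only measure tied by name to acceptability, and as planned they do not reach anyone who withdraws. At the anticipated retention this is up to 10 of 40 participants, with 8 at 80% and 4 at 90%, on the assumption that all losses are withdrawals.

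The themes will therefore come mainly from those who stayed. That those who leave hold less favourable views is a reasonable expectation, but the documents give no figure for it. The quantitative feasibility measures and the strength comparison are not shown to be affected. This is a modest weakness with a cheap remedy, and it has to be settled in the protocol and consent wording before participants begin to leave.

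**What to change.** 1. In Protocol section D (Primary Outcome), offer the exit interview to every randomised participant: at the end of the study for those who stay, and at the point of withdrawal for those who leave early and agree.
2. In Protocol section E, item 9 (Withdrawal), state that this consented interview may take place before data collection ends. State also that stopping the exercise or the supplement alone is not withdrawal from the study, so that such participants are still invited to follow-up testing and interview.
3. Report withdrawal reasons by arm beside the interview themes, with the number interviewed out of the number randomised.

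The cost is an IRB wording change and up to about 10 interviews brought forward, with no new staff or procedure. Some who leave will decline, so the gap will narrow but may not close.
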